#### POCT methods

aFor *Ct* and *Ng*, self-collected urine samples are analyzed using the *Cepheid GeneXpert®* molecular test, administered by RAs. Results are reported as positive or negative for *Ct* and/or *Ng* and shared with the attending health practitioner. The test is validated and demonstrates high sensitivity and specificity [22].bFor the initial diagnostic approach to *Tv* and BV, each participant self-collects a vaginal discharge sample using a swab. The RA then measures the pH of the sample; if the pH is above 4.5, a drop of potassium hydroxide (KOH) is added to perform the whiff test, where a fishy odor indicates a positive result [23]. The health practitioner is subsequently informed of the pH level (above or below 4.5) and whether the whiff test result is positive or negative.cFor the diagnostic approach after protocol adaptation (see 2.5.4); for VD with pH > 4.5 and a negative whiff test, an antigen-based Tv test (*OSOM®*) is applied. Results from this test (positive/negative) are shared with the health practitioner.

#### Protocol adaptation for Tv testing

An unplanned interim analysis was conducted after 218 participants had been enrolled, prompted by concerns that many laboratory-confirmed *Tv* cases had not received treatment due to negative POCT results. Without unblinding or compromising randomization, only the POCT results and gold standard laboratory results for *Tv* were compared. This analysis showed low sensitivity of the pH and whiff test: initial POCT approach (3.7% correctly identified; 7.8% false negatives). For ethical reasons, affected participants were traced and treated, and an additional diagnostic step was added for the remainder of the trial (see “ POCT methods” section).

Although *OSOM®* is a validated diagnostic tool for *Tv* detection, its sequential use following pH and whiff testing has not previously been evaluated [25].

#### Comparisons

The trial compares the accuracy of antibiotic prescriptions between the current /syndromic and POCT-guided treatment arms. It also evaluates whether the addition of educational and psychosocial support improves adherence to treatment recommendations, influences health-seeking behavior, and affects symptom resolution and patient satisfaction.

#### Implementation and adherence strategies

Before the trial began, participating health practitioners received brief training on study procedures, POCT accuracy, and updates to Nepal’s national syndromic management guidelines for STIs. This training is repeated twice during the trial.

To ensure ethical standards of care, participants in all arms who test positive for an STI via gold-standard laboratory tests are offered appropriate treatment, even if this was not prescribed initially.

As POCT procedures may prolong clinic visits by up to two hours, participants are offered refreshments during the waiting period.

HPs are free to provide any concomitant care as they find indicated and shall assess the participants independently of the study.

### Outcomes

The primary outcome measures are:The proportion of participants overtreated with antibiotics at the primary consultation with the health practitioner Overtreatment is defined as receiving a cephalosporin and/or macrolide when *Ng* is negative; a tetracycline or macrolide when *Ct* is negative; or a nitroimidazole when the gold standard test for *Tv* or BV is negative, (medications as specified in the Nepali STI case management guidelines) [15] (comparing arm 1 with the combined arms 2 and 3).The proportion of participants prescribed AMR driving antibiotics (Cephalosporins, Azithromycin, Ciprofloxacin) at the primary consultation with the health practitioner. comparing treatment as usual (arm 1) with POCT-based treatment (arms 2 and 3).The proportion of participants adhering to treatment recommendations, comparing arms 2 and 3. Adherence is assessed during telephone follow-ups after one month and is defined as follows: (a) participants report that they took the prescribed medication; (b) no additional purchase of antibiotics; and (c) no purchase of other medication for VD.

The study also examines six secondary outcome measures at various time points. The baseline data from this trial will also contribute to the analysis of the epidemiology of VD and infection including psychosocial factors, and measure the diagnostic accuracy of the POCT.

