### Interventions

#### Overview and rationale

The intervention targets the most clinically significant pathogens associated with abnormal VD: *Ct, Ng, Tv*, and BV. Untreated *Ct* and *Ng* can lead to serious health consequences, while overtreatment is associated with growing AMR. Although *Tv* and BV typically cause less severe complications, they impose a high symptom burden and are common among women presenting with bothersome VD. Both are treated with the same narrow-spectrum antibiotic, which is less likely to cause AMR [14, 36].

The intervention combines a highly accurate molecular test for *Ct* and *Ng* and a simpler POCT for *Tv* and BV, aiming to optimize diagnostic performance and resource use in Nepalese healthcare settings.

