### Protocol non-adherence and missing data

Protocol non-adherence is defined as participants in the intervention arms (arms 2 and 3) receiving antibiotics to treat *Ct*, *Ng*, *Tv,* or BV despite negative POCT results. These cases will be described in groups according to the three antibiotic treatment categories used: (a) treatment for *Ct*, (b) treatment for *Ng,* and (c) treatment for *Tv* and BV.

The proportion of missing data will be reported, and efforts will be made to determine the reason for missingness. The primary analyses will be complete case analyses. Two of the primary endpoints are registered immediately after the intervention and will not be subject to any substantial missingness. The third primary outcome is recorded at 4 weeks post-intervention and may have a greater risk of missingness. Multiple imputation methods will be considered if this missingness exceeds 20%.

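### The primary overtreatment rule counts a macrolide as overtreatment when either Ct or Ng is negative, and its Tv/BV clause can be read the same way

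*Protocol article*

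**What the plan says.** The Outcomes section builds the first primary endpoint from three alternative triggers, in one sentence that includes "receiving a cephalosporin and/or macrolide when *Ng* is negative; a tetracycline or macrolide when *Ct* is negative; or a nitroimidazole when the gold standard". Taken apart, the triggers are:

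- Ng clause: "receiving a cephalosporin and/or macrolide when *Ng* is negative".
- Ct clause: "a tetracycline or macrolide when *Ct* is negative".
- Tv/BV clause: "or a nitroimidazole when the gold standard test for *Tv* or BV is negative".

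Meeting any one clause makes the participant overtreated. Arm 1 is compared with Arms 2 and 3 combined. The cited national guideline is invoked for which medications count, not for how the clauses combine. Nowhere does the article excuse a drug under one clause because another infection is positive.

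Two other places bear on the third clause. Overview and rationale says of Tv and BV: "Both are treated with the same narrow-spectrum antibiotic". The section on protocol non-adherence sorts antibiotic treatment into three categories, the last being "c) treatment for *Tv* and BV".

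**The concern.** Macrolides sit in two clauses, and each clause looks at one test only. For a woman with Ct alone who is given a macrolide, the Ct clause raises no flag and the Ng clause does. For a woman with Ng alone given a macrolide, the roles reverse. The clauses contradict each other on the same prescription, and the joining logic settles it as overtreatment.

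The third clause raises a similar question. If one negative test is enough, a woman with BV alone or Tv alone who receives the shared drug is scored as overtreated.

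At stake is the size of the primary risk difference. Arms 2 and 3 aim to direct drugs to test-positive women, and those are the women such a rule miscounts. In Arm 1 many of the same women are already flagged through another clause, so the miscount is smaller there. The Comparisons section says the trial compares how accurate prescriptions are; a rule that marks down accurate prescribing works against that.

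**Working it through.** **1. The plan's own figure.** Sample size gives at least 90% power at a significance level of 0.017 for differences of 10 to 20 points, with overtreatment near 85%. For 85% v 75%, 500 v 1000 women:

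- pooled p = (500×0.85 + 1000×0.75)/1500 = 0.7833
- standard error under no difference = √[0.7833×0.2167×(1/500 + 1/1000)] = 0.02256
- standard error under the alternative = √(0.85×0.15/500 + 0.75×0.25/1000) = 0.02104
- power = Φ[(0.10 − 2.387×0.02256)/0.02104] = 98.6%; 95% interval width = 2×1.96×0.02104 = 8.2 points

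The stated power is reproduced for this outcome.

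**2. The rule applied to single profiles.**

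| Infection and drug | As written, either negative | As written, Tv/BV clause = both negative | Every assigned infection negative |
|---|---|---|---|
| Ct only, macrolide | overtreated | overtreated | not |
| Ng only, cephalosporin + macrolide | overtreated | overtreated | not |
| BV only, nitroimidazole | overtreated | not | not |
| Tv only, nitroimidazole | overtreated | not | not |
| Ct only, tetracycline | not | not | not |
| Ng only, cephalosporin | not | not | not |
| Ct + Ng, cephalosporin + macrolide | not | not | not |
| Tv + BV, nitroimidazole | not | not | not |
| No infection, nitroimidazole | overtreated | overtreated | overtreated |

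**3. Inputs for the arm contrast.**

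- From the article: Tv 3.7% + 7.8% = 11.5% (Protocol adaptation for Tv testing, if both are shares of the 218 enrolled); BV test sensitivity and specificity set at 87% (Background says above 87%).
- Assumed: BV 15 to 35%, Ct 3%, Ng 1%, infections independent; Tv detection 90% in Arms 2 and 3; prescribing there follows the test results, with a macrolide for every Ct-positive woman; Arm 1 prescribes a nitroimidazole to 70% or 80% and a cephalosporin plus macrolide to 50%, regardless of infection.

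**4. One case in full (BV 15%, Arm 1 nitroimidazole 70%).**

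Shares: BV only 0.15×0.885 = 0.1328; Tv only 0.115×0.85 = 0.0978; neither 0.885×0.85 = 0.7523; both 0.115×0.15 = 0.0173.

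Arms 2 and 3:
- A nitroimidazole goes to 0.87 of BV only, 1 − 0.87×0.10 = 0.913 of Tv only, and 0.13 of neither.
- Literal flag from nitroimidazole = 0.1328×0.87 + 0.0978×0.913 + 0.7523×0.13 = 0.3025. Adding Ct-positive, Ng-negative women not yet flagged: 0.03×0.99×(1 − 0.3025) = 0.0207. Total 32.3%.
- Corrected = 0.7523×0.13 = 9.8%.

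Arm 1:
- Literal = 1 − (1 − 0.5×0.9997)(1 − 0.7×0.9828) = 84.4%, where 0.9997 = 1 − 0.03×0.01 and 0.9828 = 1 − 0.0173 (before rounding).
- Corrected = 1 − (1 − 0.5×0.99)(1 − 0.7×0.7523) = 76.1%.

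Risk difference: literal 84.4 − 32.3 = 52.1; corrected 76.1 − 9.8 = 66.3. Shrinkage 14.2 points.

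With the Tv/BV clause read as both negative: Arm 1 76.3%; Arms 2 and 3 0.0978 + 0.0297×(1 − 0.0978) = 12.5%; difference 63.9 (unrounded). Shrinkage 66.3 − 63.9 = 2.4 points.

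**5. Across BV prevalence (risk differences in points).**

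| BV | Arm 1 nitroimidazole | Literal | Corrected | Shrinkage, literal | Shrinkage, Tv/BV clause = both negative |
|---|---|---|---|---|---|
| 15% | 70% | 52.1 | 66.3 | 14.2 | 2.4 |
| 15% | 80% | 57.0 | 70.1 | 13.1 | 2.5 |
| 25% | 70% | 46.3 | 64.3 | 18.0 | 2.4 |
| 25% | 80% | 51.2 | 67.7 | 16.5 | 2.5 |
| 35% | 70% | 40.6 | 62.4 | 21.8 | 2.5 |
| 35% | 80% | 45.4 | 65.3 | 19.9 | 2.5 |

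**6. Two checks.** If every Ct-positive woman in Arms 2 and 3 receives a tetracycline, the last column falls to between −0.3 and −0.2 points, in effect zero. The Background figure of about one-third with any of the four conditions fits BV near 1 − 0.667/(0.885×0.97×0.99) = 22%. BV at 35% would give 1 − 0.65×0.885×0.97×0.99 = 45% with any condition, so the top of the range is the least supported.

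**The case against.** The strongest reply concerns the Tv/BV clause, which carries most of the size. In ordinary English its wording can mean that neither test is positive. The article leans that way, since it says one drug treats both conditions and groups them as one treatment category. This stands: the clause is an ambiguity, not a settled scoring error.

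The macrolide part can also be small. Background names both azithromycin and doxycycline, and the guideline that fixes the medications is not available here. If Ct is treated with a tetracycline, the effect is close to nil. That stands for the size but leaves the wording in contradiction.

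The article is a condensed protocol, and an analysis plan may spell out the derivation. That is possible, but the article does not leave the rule open. It prints one, and the macrolide clauses as printed conflict.

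Three stronger inferences do not hold:

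- A reader might infer that only women with dual infections escape the flag. The profile table shows otherwise: Ct only with a tetracycline and Ng only with a cephalosporin also escape.
- A reader might take the literal overtreatment rate in Arms 2 and 3, above 30% in these scenarios, as the bias. It is a single-arm rate. Literal scoring also raises Arm 1, by 84.4 − 76.1 = 8.3 points in the worked case, so the contrast moves less.
- A reader might infer that the trial loses power or risks a false positive. In every scenario in the table, power stays near 100% and the bias is toward no difference.

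**Conclusion.** The point holds, in two parts of different strength. The macrolide overlap is a literal logic error in a primary outcome. The Tv/BV wording is an ambiguity whose likely intent is that both are negative, but the article does not say so.

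The effect is an understated risk difference. If the Tv/BV clause is applied literally, the shrinkage is about 14 to 22 points with Arm 1 nitroimidazole prescribing at 70%, and about 13 to 20 points at 80%. For BV of 15 to 25%, which fits the article's own one-third figure better, it is about 14 to 18 points at 70% prescribing. If the clause means both negative, it is about 3 points or less, and near zero if Ct-positive women receive a tetracycline.

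These sizes rest on assumed BV, Ct and Ng prevalence, independence of infections, Tv detection of 90% and the assumed prescribing in each arm. The logic error rests on none of them. The gap between the two readings is comparable with the 10 to 20 point difference in Sample size, so the reading should not be left to whoever writes the derivation code.

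**What to change.** Restate the derivation before the statistician is unblinded. This is a rule for scoring the outcome only, not a rule for treating patients. A drug class counts as overtreatment only when every infection the article assigns to it is gold-standard negative:

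- cephalosporin: Ng negative
- tetracycline: Ct negative
- macrolide: both Ct and Ng negative
- nitroimidazole: both Tv and BV negative

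A participant is overtreated if any class is flagged. Date and record the restatement, so that it cannot be taken as a response to results.

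The cost is rewording the definition, including a separate macrolide line, and the matching derivation code. Prescriptions and gold-standard results are already part of data collection, so no new data are needed. Trial status reports recruitment complete, and Randomization and blinding says the statistician is blinded to allocation, so the change can be made cleanly if that is still the case.

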### Sample size

Based on the study objectives, recruitment feasibility, and the desired precision of estimates (i.e., two-sided 95% confidence intervals [CIs]), the sample size was calculated using PASS Sample Size software. Antibiotic use will be compared between both Arm 2 and Arm 3 versus Arm 1 (*N* = 1500) at the first consultation and will serve as a secondary outcome. The effect of the educational measures on the use of OTC antibiotics will be compared between Arm 2 and Arm 3 (*n* = 1000) at 4 weeks and 4 months of follow-up.

It is estimated that approximately 85% of women in LLMICs are over-treated with antibiotics for VD, and around 50% receive antibiotics that contribute to AMR. Furthermore, about 40% of women are expected to purchase antibiotics OTC. The overtreatment with antibiotics and the use of AMR will be assessed at the first consultation whilst the adherence to the treatment recommendation will be assessed at 4 weeks as primary outcome and at 4 weeks and 4 months of follow-up as secondary outcome.

With 1500 participants randomized equally across the three arms (allocation ratio of 1:1:1), a 10–20 percentage point difference between groups in any of these measures will produce CIs with a width of 8–12%, achieving at least 90% power for each comparison at a significance level of 0.017 (adjusted from 0.05 to account for multiplicity with three primary outcome measures). For the assessment of over-the-counter antibiotic use, even with a 40% loss to follow-up, the expected CI width remains around 15%.

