#### Primary outcome analyses

Two of the three primary endpoints (a) the proportion of participants overtreated with antibiotics and (b) the proportion of participants being prescribed AMR-driving antibiotics will be compared between groups (Arm 1 *vs* Arm 2 + 3). The third primary endpoint, (c) the proportion adhering to treatment recommendations at 1 month follow-up, will be compared between groups Arms 2 vs 3. The risk difference and corresponding 95% confidence intervals, as well as p-values calculated from chi-squared tests, will be reported. *P*-values below 0.017 will be regarded as statistically significant due to there being three primary outcomes.

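### The claim of at least 90% power at a 10–20 point difference is not supported for the third primary outcome: the sample-size section's only rate for Arm 2 vs Arm 3 is for OTC antibiotic purchase, a secondary outcome, and at 10 points power for the composite is about 78–82% before loss to follow-up.

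*Protocol article*

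**What the plan says.** **Definition and test.** The Outcomes section defines adherence by three conditions joined by a conjunction: "a) participants report that they took the prescribed medication; (b) no additional purchase of antibiotics; and (c) no purchase of other medication for VD". The Primary outcome analyses section tests it: "The third primary endpoint, (c) the proportion adhering to treatment recommendations at 1 month follow-up, will be compared between groups Arms 2 vs 3". The criterion is p < 0.017, because there are three primary outcomes.

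**Sizing.** The Sample size section describes the comparison of the two POCT arms differently: "The effect of the educational measures on the use of OTC antibiotics will be compared between Arm 2 and Arm 3", with n = 1000. It gives three rates. Two belong to the prescribing outcomes: "approximately 85% of women in LLMICs are over-treated with antibiotics for VD, and around 50% receive antibiotics that contribute to AMR". The third is "about 40% of women are expected to purchase antibiotics OTC". The section then says that adherence is the primary outcome at 4 weeks and a secondary one at 4 weeks and 4 months, without a rate. Next it states that "a 10–20 percentage point difference between groups in any of these measures will produce CIs with a width of 8–12" per cent, with at least 90% power for each comparison at 0.017. Finally, for OTC use, it allows 40% loss to follow-up and expects a width of about 15%.

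**Status of OTC acquisition.** The Abstract lists it among the secondary outcomes, and the Subgroup analysis section calls the Arm 2 vs 3 comparison of it secondary.

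**The concern.** The composite and OTC purchase are different endpoints. A woman who buys no antibiotic but does not take what was prescribed, or who buys another remedy for discharge, counts as a non-purchaser on the OTC measure and as non-adherent on the composite. Component (b) is also not limited to purchases without a prescription. A rate for OTC purchase therefore does not fix a rate for adherence, and a difference on one is not automatically the same difference on the other.

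What is at stake is a stated figure. A reader of the trial report will take from the protocol that the Arm 2 vs 3 primary comparison had at least 90% power at a 10-point difference. If that is wrong, a non-significant result on the third primary outcome may be read as stronger evidence of no worthwhile effect than the design supports.

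**Working it through.** **Inputs from the Sample size section:** 1500 randomised 1:1:1, so 500 per arm; significance level 0.017 (taken as two-sided, z = 2.387); rates 85%, 50% and 40%; difference 10–20 points; 40% loss, leaving 500 × 0.6 = 300 per arm.

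**Formulas.** With d the difference, power = Φ[(d − 2.387·SE₀)/SE₁]. SE₀ uses the pooled proportion and SE₁ the two separate proportions. The 95% interval width is 2 × 1.96 × SE₁.

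**Step 1: reproduce the plan's figures at a 10-point difference.**

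| Comparison | n | Power at 0.017 | 95% CI width |
|---|---|---|---|
| Overtreatment, 85% to 75% | 500 vs 1000 | 98.6% | 8.2% |
| AMR-driving antibiotics, 50% to 40% | 500 vs 1000 | 90.2% | 10.7% |
| OTC purchase, 40% to 30% | 500 vs 500 | 82.5% | 11.8% |
| OTC purchase, 40% to 30% | 300 vs 300 | 57.2% | 15.2% |

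For the third row:
- SE₀ = √(0.35 × 0.65 × 2/500) = 0.03017.
- SE₁ = √((0.40 × 0.60 + 0.30 × 0.70)/500) = 0.0300.
- (0.10 − 2.387 × 0.03017)/0.0300 = 0.933, and Φ(0.933) = 82.5%.

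The interval widths match the text on the OTC rate, including the figure of about 15% after loss. The 90% power holds for the two prescribing outcomes. It does not hold for Arm 2 vs 3 at 10 points even on OTC purchase, where 90% would need 610 per arm. At a significance level of 0.05 the same OTC comparison would have 91.4%.

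**Step 2: the composite.** The protocol gives no adherence rate, so a range must be assumed. If component (b) fails for the 40% who purchase OTC, Arm 2 adherence cannot exceed 100% − 40% = 60%, and failures on (a) or (c) lower it. I take 30–60%. Applying the 40% loss to adherence is also an assumption, since the text states it for OTC use.

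| Arm 2 adherence, 10-point rise | Power, 500 per arm | Power, 300 per arm |
|---|---|---|
| 30% to 40% | 82.5% | 57.2% |
| 40% to 50% | 78.7% | 53.0% |
| 45% to 55% | 78.2% | 52.5% |
| 50% to 60% | 78.7% | 53.0% |
| 60% to 70% | 82.5% | 57.2% |

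With 400 per arm (20% loss) the range is 67–72%. Reaching 90% needs 610–671 analysed per arm.

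**Step 3: where the claim does hold.** Over the same range of rates, the difference detectable with 90% power is about 11.0–11.6 points with 500 per arm and 14.0–14.9 points with 300. A 15-point composite difference has over 99% power with 500 per arm and 90–94% with 300. A 20-point difference has over 99% in both cases.

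**Sensitivity to the 60% cap.** If Arm 2 adherence were 70%, a 10-point rise would have 89.9% power with 500 per arm and 67.2% with 300; at 80%, 98.0% and 85.4%.

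**The case against.** The best reply is that the Sample size section does name adherence as the 4-week primary outcome immediately before the sentence on 10–20 points, and splits the significance level over three primary outcomes. The phrase about any of these measures may therefore include adherence. That stands: a reader might infer that adherence was left out of the sizing, or that the difference was stated only for another endpoint, and the text does not support so firm a reading. But including adherence does not rescue the claim. No adherence rate is given, and at 10 points the power is below 90% across the assumed range.

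A reader might also infer that a null composite would hide a real effect on OTC purchase. It would not. OTC acquisition is a separate secondary outcome compared between Arms 2 and 3, and the Secondary outcome analyses section gives binary secondary outcomes the primary strategy: risk difference, interval and chi-squared test.

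Nor do the documents show that the comparison is underpowered in general. How far an OTC effect carries into the composite depends on how components (a) and (c) behave in each arm, on which they give no figures. If 80% of non-purchasers met (a) and (c) in both arms, OTC effects of 15 and 20 points would become 48% vs 60% and 48% vs 64%, with power of 92% and 99.7% at 500 per arm. If the support also improved (a) or (c), the composite effect could exceed the OTC effect.

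Finally, recruitment was completed before this version, so restated power changes neither the test nor the estimate, and the reported interval will show the precision achieved. That limits the consequence but does not make the stated figure right.

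**Conclusion.** The point holds as an unsupported power statement. The outcome definition and the planned test agree with each other; the Sample size section does not support the power it claims for them. Its numerical basis for Arm 2 vs 3 is a secondary outcome that overlaps with one of the three components.

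At the 10-point end of its own range, power for the composite is about 78–82% with 500 per arm and about 52–57% with 300, against a stated minimum of 90%. These figures assume Arm 2 adherence of 30–60%, a two-sided 0.017 level, the normal approximation and, for 300 per arm, that the 40% loss stated for OTC use applies to adherence. The 60% ceiling further assumes that component (b) fails at the 40% OTC rate. At about 15–20 points on the composite the claim can be met, even after that loss.

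**What to change.** In the Sample size section:

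1. Label the 40% purchase rate, the 40% loss allowance and the 15% interval width as support for the secondary outcome of OTC antibiotic acquisition.
2. For the third primary outcome, state an assumed Arm 2 adherence rate, and restate power and detectable difference for the composite at 0.017, both with 500 per arm and after loss to follow-up.
3. Limit the statement of at least 90% power at 10 points to the two prescribing outcomes, where it reproduces.

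With Arm 2 adherence assumed at 30–60%, the restated detectable difference at 90% power would be about 11–12 points with 500 per arm and 14–15 points with 300.

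The cost is a few sentences and a less favourable stated power for one primary outcome. Enrolment, the outcome definition, the planned test and data collection stay as they are.
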